## Abstract

**Background:**

Knee osteoarthritis (KOA) is considered a whole-joint disease that is amenable to prevention and treatment in the early stages. Exercise is among the core treatment recommendations for KOA and it has been suggested that optimal exercise regimens should improve aerobic capacity and knee extensor strength. Subchondral bone and articular cartilage are functionally paired, and information on the responses of these tissues to exercise may help in the development of efficacious and feasible exercise regimens that can potentially improve bone and cartilage properties. This article describes a clinical trial investigating the effects of a multicomponent exercise regimen on the subchondral bone and articular cartilage of the knee joint in postmenopausal women with mild KOA.

**Methods:**

A minimum of 90 postmenopausal women between the ages of 55 and 75 meeting the inclusion criteria will be recruited. After an initial assessment, the participants will be randomly assigned to two groups. The intervention group will participate in a progressive multicomponent exercise regimen, including step aerobics and resistance training alternating every 2 weeks, for 50 min three times a week for 8 months. The reference group will be conducting home exercise program representing standard rehabilitative management for KOA patients. The primary outcome measures of this trial are the 8-month changes in the biochemical composition of the knee articular cartilage measured by the T1r and T2 relaxation times from quantitative magnetic resonance imaging and subchondral bone sclerosis, density and structure as measured via cone beam computed tomography. Measurements will be performed at baseline, after the 8-month intervention period, and at 12 months of maintenance.

**Discussion:**

This RCT investigates the effectiveness of a multicomponent exercise regimen on the subchondral bone and cartilage of the knee joint and the potential interaction between these tissues. The information gained will improve our understanding of the effects of exercise on subchondral bone and the biochemical properties of articular cartilage and improve the prescription of multicomponent exercise regimens in the management of mild KOA.

**Trial registration:**

ClinicalTrials.gov NCT06173193. Retrospectively registered before completion of the recruitment on 31 October 2023, https://www.clinicaltrials.gov/study/NCT06173193.

**Supplementary Information:**

The online version contains supplementary material available at 10.1186/s13063-025-08928-1.

## Introduction

Knee osteoarthritis (KOA) is considered a whole-joint disease that is amenable to prevention and treatment in the early stages [1]. Symptoms of this disease include pain around the knee joint, loss of range of motion, grinding and popping sounds from the joint, and muscle weakness [2]. These symptoms may cause difficulties in daily activities such as walking, climbing stairs, and performing household chores, which can lead to a decreased quality of life [3]. As the prevalence of KOA is high, being approximately 23% globally in individuals aged 40 years and over [4], it places a considerable burden on individuals as well as societies [5]. Risk factors for this disease include age, obesity, female sex, repeated stress on the joint, muscle weakness, and previous knee injuries [6, 7].

In the Osteoarthritis Research Society International and European Society for Clinical and Economic Aspects of Osteoporosis, Osteoarthritis and Musculoskeletal Diseases KOA guidelines, the core set of nonpharmacological treatments includes patient education, weight loss for overweight, and a structured exercise program [8, 9]. It has been suggested that optimal exercise programs should improve aerobic capacity and knee extensor strength, and the program should be carried out three to five times a week, with each session lasting an hour [10, 11]. However, despite its broad application, the impact of exercise loading on knee joint tissues in humans is poorly understood, and the benefits of exercise for pain and physical function are small and thus of questionable clinical importance [12].

Current evidence suggests that subchondral bone is actively involved in osteoarthritis (OA) development and that bone and articular cartilage are functionally coupled either through the distribution of joint loads or the exchange of signaling molecules between the tissues [13–15]. Exercise has good potential for improving bone traits by enhancing bone mass, structure, and strength at loaded sites across the age spectrum, as well as appearing safe for articular cartilage, and thus could be an important regimen for overall joint health to reduce the progression of OA [16–22]. Accumulating evidence suggests that osteogenic changes in subchondral bone develop before articular cartilage degeneration and that vascularization from subchondral bone to articular cartilage plays a significant role in cartilage erosion in OA [13]. To date, in humans, the effects of exercise on the interplay of articular cartilage and subchondral bone have not been studied. Furthermore, emerging evidence suggests that physiological joint loading could be used to counteract the inflammatory pathways and restore anabolic activities [23]. Biological pathways within a joint are mechanosensitive, and biomechanical factors, such as exercise loading, are modifiable and represent a potential means of intervention.

Quantitative magnetic resonance imaging (qMRI) and cone beam computed tomography (CBCT) allow detailed investigation of articular cartilage and subchondral bone and the effects of moderate-intensity exercise on them [24–31]. In this randomized controlled trial, we plan to investigate the effects of an 8-month joint loading exercise regimen on knee joint subchondral bone morphology and properties, articular cartilage morphology and biochemical alterations, and their 12-month maintenance in women with mild KOA. Furthermore, we will examine the effects of exercise regimen on molecular biomarkers related to OA and inflammation, bone traits, physical function, performance, body composition, and clinically important OA-related symptoms. We will assess changes in these variables after the 8-month intervention, which is the primary timepoint. In addition, we will investigate whether the potential benefits of exercise will be maintained 1 year after the training period. The treatments that will be provided to members of a reference group comply with the current standard rehabilitative management for knee OA patients [32]. The aim of this article is to describe a randomized controlled trial that will investigate the effects of a multicomponent exercise intervention on subchondral bone and articular cartilage in postmenopausal women with mild knee OA.

## Methods and analysis

### Study design

This 20-month study will be an 8-month randomized controlled exercise intervention trial (RCT) with two parallel groups and a subsequent 12-month follow-up after the intervention. After baseline measurements, the participants will be randomly assigned to one of two study arms: a multicomponent exercise group or a reference group. All outcome measures will be performed at baseline, after the 8-month intervention, and at follow-up 12 months after completion of training. The primary outcome measures will be assessed separately, although they assess the same phenomena from different perspectives. The study will be conducted in two separate phases for practical reasons. Recruitment of the participants started in June 2023, and the data collection will be finished by March 2026. All of the data collection will take place at the University of Jyväskylä and Hospital Nova. The protocol described in this study is version 1.0, finalized on October 16, 2024.

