### Sample size

Sample size and power calculations were estimated for the T2 relaxation time endpoints (s) of this study using Stata (StataCorp, College Station, TX and SPSS, IBM Corporation), as no adequate a priori data exist on subchondral bone or T1ρ estimates in exercise intervention studies. The sample size was evaluated using simulation-based sample size, because no accurate and reliable data was available to make an estimate. The starting values for the simulation were based on data from our previous studies [17, 18]. It is estimated that for 80% statistical power, 38 participants are needed in each group to detect a mean difference of 4 ms in T2 between the groups at significance level of *p* < 0.05. The dropout rate at the 12-month follow-up is estimated to be approximately 15% based on our previous studies [17, 35], so at least 90 participants will need to be recruited.

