### Primary outcomes

#### Magnetic resonance imaging

qMRI contrast mechanisms will be used to assess the tibiofemoral and patellofemoral articular cartilage. Co-primary qMRI outcomes will be T1ρ and T2 relaxation time mapping which will be further enhanced through a texture analysis. qMRI can be used to reveal the architecture of the articular cartilage and indirectly alterations in its mechanical properties [28]. T1ρ and T2, in particular, are sensitive to biochemical changes in cartilage [29–31]. Previous studies have shown that the severity of radiographic knee OA and histological degeneration of cartilage are associated with increased T2 values [31, 36]. In vivo test–retest reliability for T2 measurements, expressed as coefficients of variation (CV), has been reported to vary from 2.3 to 6.5% and from 2.3 to 6.1% for T1ρ [37].

The estimated cartilage glycosaminoglycan content will be measured using T1ρ. T2 relaxation time mapping will be used to provide information about cartilage quality, with longer times reflecting a decrease in collagen matrix integrity and an increase in water content, which are associated with cartilage degeneration [31, 38]. Furthermore, the qMRI measurements will be further enhanced through a texture analysis approach [39] where spatial relationships and texture patterns will be analyzed from tibiofemoral cartilage. Morphometric analysis will be used to analyze articular cartilage thickness and volume.

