### Statistical analysis

Data will be analyzed with an intention-to-treat strategy, where all the enrolled participants will be included in the analysis in their randomized groups, regardless of protocol adherence. The mean change from baseline in the outcomes will be compared between the groups. One-way analysis of covariance (ANCOVA) with the 8-month endpoint and 12-month follow-up measurements as dependent variables will be used to assess the intervention effect between the groups. Cartilage and bone traits as outcome variables will be adjusted for baseline values, age, height, and body mass. In the association analyses, correlation coefficients will be calculated via the Pearson or Spearman methods with bootstrap-type confidence intervals. In addition, generalized linear models (GLM) with appropriate distributions and link functions will be provided for each outcome. Compliance with the intervention will be calculated using the following formula: [number of exercise sessions performed]: [expected number of exercise sessions] × 100. Statistical analyses will be performed using up-to-date versions of statistical software (Stata, StataCorp, College Station, TX and SPSS, IBM Corporation). Two-sided *p* values with alpha < 0.05 will be used for all tests, and 95% confidence intervals will be provided when the results are presented. A professional academic statistician blinded to the study groups will conduct the analyses.

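### Several primary outcomes are each tested at two-sided 5% with no deciding endpoint, so the familywise error rate is not controlled, and the 80% power belongs to one T2 comparison only

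*Protocol article*

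**What the plan says.** **Primary outcomes.** Table 2 puts T1ρ and T2 of tibiofemoral and patellofemoral cartilage, texture analysis, cartilage thickness and volume, and the CBCT variables BMD, BMC and joint space narrowing under one primary heading. The Magnetic resonance imaging section states: "Co-primary qMRI outcomes will be T1ρ and T2 relaxation time mapping". That section also describes segmenting medial and lateral tibial and femoral regions plus a further slice at the thickest cartilage. It does not say whether regions are averaged or tested one by one.

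**Testing.** Study design: "The primary outcome measures will be assessed separately, although they assess the same phenomena from different perspectives". Statistical analysis: "Two-sided *p* values with alpha < 0.05 will be used for all tests". It compares groups by baseline-adjusted ANCOVA and adds generalized linear models for each outcome. The Introduction fixes 8 months as the primary timepoint.

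**Sample size.** At p < 0.05 and 80% power, "38 participants are needed in each group to detect a mean difference of 4 ms in T2 between the groups". The section explains that usable earlier data were lacking for T1ρ and subchondral bone. No SD and no cartilage region are given.

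**The concern.** With several outcomes called primary, each examined separately at 5%, nothing says which result decides the trial or how a mixture of significant and non-significant results is to be read. A false-positive finding in one variable could be reported as a primary result, with a probability well above 5% that at least one such finding occurs. The word co-primary does not settle this, because the article does not say whether both relaxation times must succeed or whether either is enough. Nor does the power statement help, since it concerns one T2 comparison. A reader who sees 5% and 80% beside a list of primaries could take both figures to describe the trial's primary claim.

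**Working it through.** **1. The plan's own figure.** 38 per group is 76 evaluable. With 15% loss, 76 / 0.85 = 89.4, so 90 recruited. The recruitment target follows.

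The 38 itself cannot be reproduced, because no SD is stated ("The starting values for the simulation were based on data from our previous studies"). Solving backwards with the normal approximation: d = (1.960 + 0.842) × √(2/38) = 0.643, so SD = 4 / 0.643 = 6.22 ms. With a t-test, d = 0.651 and SD = 6.14 ms. These values are assumptions and are used only in step 4.

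**2. Number of primary tests.** The count depends on how Table 2 is read:
- 2: T1ρ and T2 only, one test each.
- 5: T1ρ, T2, BMD, BMC, joint space narrowing.
- 8: the five above plus texture, thickness and volume, one test each.
- 13: T1ρ and T2 in five regions (four tibiofemoral, one patellofemoral) plus three CBCT variables, 5 × 2 + 3.

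**3. Chance of at least one false-positive primary.** For independent tests this is 1 − 0.95^k. For correlated tests, k equicorrelated normal statistics were simulated (400,000 draws) and the share with any absolute value above 1.96 was counted. No SD is needed.

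| k | Independent | Correlation 0.5 | Correlation 0.8 |
|---|---|---|---|
| 2 | 9.8% | 9.0% | 7.8% |
| 5 | 22.6% | 18.3% | 12.7% |
| 8 | 33.7% | 24.9% | 15.8% |
| 13 | 48.7% | 33.4% | 19.3% |

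Every entry exceeds 5%.

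**4. Power if the family is controlled.** Take 38 per group and assume every outcome has the back-solved d. Power at level 0.05/k is approximately Φ(d√(38/2) − z), with d√19 = 2.802:
- k = 2: z = 2.241, Φ(0.560) = 71%.
- k = 3: z = 2.394, Φ(0.408) = 66%.
- k = 5: z = 2.576, Φ(0.226) = 59%.

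These are Bonferroni values. Holm starts at the same level and can only do better, so they are lower bounds for Holm.

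**5. If co-primary means both must succeed.** There is then no inflation over T1ρ and T2. But if each had 80% power and the tests were independent, joint power would be 0.8 × 0.8 = 64%. The article gives no basis for 80% on T1ρ.

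**The case against.** **Multiplicity detail is often left to an analysis plan, which is not shown.** True in general. But this point does not rest on silence: the article states both separate assessment and 0.05 for all tests.

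**Separate tests may serve separate claims about cartilage and bone, and whether such claims need joint control is debated.** This is a fair position. The article does not state it, and it would not cover several variables within one tissue.

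**The outcomes are said to view the same phenomena, so they are correlated.** This stands in part. Correlation lowers the rate, but at 0.8 it is still 7.8% for two tests.

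**The family may be small.** Also fair. Only T1ρ and T2 are called co-primary, texture is described as enhancing them, and the Abstract's primary outcomes omit texture, thickness and volume. On the other hand, the Abstract names bone sclerosis, density and structure, which do not match Table 2's CBCT variables, so the list is not settled.

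**The sample size section already limits itself to T2.** It does, openly. Only the region is missing, and the article never claims 80% for the whole family.

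**The power figures are rough.** They are. They assume a back-solved SD and the same effect for every outcome, whereas the planned analysis is baseline-adjusted. The 15% loss refers to the 12-month follow-up, so more than 38 per group may be available at 8 months. With all 45 per group, two-test power would be about 79%.

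**Stronger readings that the text does not support.** A reader might infer that no error rate is controlled at all, but each test is held at 5%. A reader might take 13 as the least possible count, but regions are segmented without being declared separate hypotheses. A reader might infer that any one significant result makes the trial positive, but no success rule is stated. A reader might say that ANCOVA and GLM compete on equal terms, but the text largely points to ANCOVA as the lead model.

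**Conclusion.** The concern holds as a point about familywise error. On every count examined, from two tests upward, the chance of at least one false-positive primary exceeds 5%: about 8–10% for 2 tests, 13–23% for 5 and 16–34% for 8. The 49% figure is the extreme case of 13 independent tests. These rates rest on the count of tests and their correlation, neither of which the article fixes, and on no assumption about the SD. The stated 80% applies to a single T2 comparison in a region still to be named and cannot be carried over to the primary family. The 71% for two adjusted tests is illustrative, because it depends on d of about 0.65 for each outcome. The 38 and the 90 are not shown to be wrong.

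**What to change.** Choose one of two routes in the protocol, analysis plan and registry entry, before any unblinded analysis:

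1. **Single primary endpoint.** Name one 8-month T2 measure, in one stated region or as a pre-specified average over regions. The sample size, the 5% level and the 80% power then stand as written for that test.
2. **Short primary list under Holm.** Name two or three measures with at least one from cartilage and one from bone, for example T2 and subchondral BMD, with or without T1ρ. State that 80% does not hold at the adjusted level: about 71% per test for two and 66% for three at 38 per group, under the assumed d. This route suits the stated interest in both tissues. A fixed sequence starting with T2 would make any bone claim conditional on the cartilage result.

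Under either route, move the remaining variables and regions to secondary or exploratory, align the Abstract with Table 2, and state that the baseline-adjusted ANCOVA at 8 months decides and the GLM is supportive.

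The cost is wording, with no new data. Fewer outcomes can be called primary, and route 2 loses some power per test. Restoring 80% for two tests would need 47 per group, or 94 / 0.85 = 111 recruited, which is not open to a trial whose recruitment is complete unless it already enrolled that many. Trial status says that phase 1 post-intervention measurements are done, so the change should be dated and recorded as made blind to group results.

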### Participants and selection criteria

Volunteer postmenopausal women between the ages of 55 and 75 will be recruited from the county of Central Finland through local newspaper advertisements. Eligibility will be initially assessed via a structured telephone interview. The telephone questionnaire includes questions about medical history, hormonal replacement therapy status, knee symptoms, and current level of physical activity. Participants who are eligible based on the telephone interview will be invited to weight-bearing radiography of both knees. An experienced fellowship-trained musculoskeletal radiologist will assess the degree of OA in the tibiofemoral joints according to the Kellgren-Lawrence (KL) grading system [33]. Participants with a KL score of I (possible osteophytes) or II (definite osteophytes, possible joint space narrowing) will progress to the next stage of eligibility assessment and undergo physiotherapy screening. Prior to the screening, participants will fill out an initial health questionnaire (Supplement 1). During the screening, any possible physical or medical limitations to full participation in the intervention will be assessed, e.g., possible physical disabilities, excessive laxity of the knee joint, severely restricted joint range of motion, and history of any illness for which exercise is contraindicated or that would limit participation in the exercise regimen. The assessing physiotherapist may refer participants to the study physician if deemed necessary for their safe participation in the study. Participants will be excluded if they meet one or more of the following criteria: body mass index (BMI) > 35 kg/m^2^, knee pain > 7 on the Numeric Rating Scale (NRS, 0–10) in the past month, known loose particles in the knee joint, acute inflammation in knee joint, intra-articular knee steroid injection or oral steroid treatment in the previous 12 months, systemic hormonal replacement therapy, undergoing treatment for osteoporosis or a *T*-score for femoral neck bone mineral density (BMD, g/cm^2^) lower than − 2.5, i.e., indicating osteoporosis as measured by dual-energy X-ray absorptiometry [34], type I diabetes, cardiac disease, kidney deficiency, diagnosed rheumatic disease (other than OA), surgical procedure on the knee (excluding partial meniscectomy or arthroscopy over 12 months ago), or joint replacement surgery in the lower limbs. Additional exclusion criteria are implanted devices that would contraindicate MRI, including electronic or ferromagnetic implants, such as pacemakers; unsuitable metals within the body; artificial aortic heart valves; metal particles in the eyes; or large tattoos on the lower limb. All participants who meet the inclusion criteria will be enrolled in the study and undergo baseline measurements. Trial’s participant selection and measurement procedures are presented in Fig. 1 and Fig. 2.

**Fig. 1 Fig1:**
[figure not shown]
Trial profile

**Fig. 2 Fig2:**
[figure not shown]
Trial flowchart

### Sample size

Sample size and power calculations were estimated for the T2 relaxation time endpoints (s) of this study using Stata (StataCorp, College Station, TX and SPSS, IBM Corporation), as no adequate a priori data exist on subchondral bone or T1ρ estimates in exercise intervention studies. The sample size was evaluated using simulation-based sample size, because no accurate and reliable data was available to make an estimate. The starting values for the simulation were based on data from our previous studies [17, 18]. It is estimated that for 80% statistical power, 38 participants are needed in each group to detect a mean difference of 4 ms in T2 between the groups at significance level of *p* < 0.05. The dropout rate at the 12-month follow-up is estimated to be approximately 15% based on our previous studies [17, 35], so at least 90 participants will need to be recruited.

